### 3.3. Study Visit

Women and their offspring born during the BEDIP-N study will receive one follow-up study visit three to seven years postpartum, which for the mother consists of a 75 g OGTT test, anthropometric measurements and questionnaires (about the mothers and their offspring) and for the child consists of fasting blood sampling and anthropometric measurements. Furthermore, baseline characteristics and data on medical and obstetric history are collected. The biological father of the child is also asked to complete a questionnaire on sociodemographic data and (family) history for cardiometabolic diseases.

#### 3.3.1. Lab Measurements

In women, after a 10 h overnight fast, hemoglobin A1c (HbA1c), C-peptide, and lipid profile (total cholesterol, triglycerides, high-density lipoprotein (HDL) and low-density lipoprotein (LDL) cholesterol) are measured, and a 2 h 75 g OGTT is performed, with measurements of glucose and insulin fasting, at 30 min, 60 min and 120 min. In offspring, fasting glycemia, HbA1c, insulin, C-peptide and lipid profile will be measured. Both in mothers and offspring, a plasma sample will be taken to allow for future analysis of plasma glycated CD59 by Harvard [name]’s lab. In addition, two extra plasma samples will be collected to allow for analysis of new (not yet defined) biomarkers in the future. In the long-term, blood samples will be stored at −80 °C in the UZ Leuven biobank.

Venous blood is collected by a nurse. For the 75 g OGTT, participants are asked to fast for at least 10 h and to not smoke prior to the test. During the test no physical activity is allowed. They are also instructed to only drink water but no other drinks with sugar or caffeine. The test starts with a fasting blood sample. After the fasting blood collection, women are instructed to consume a 75 g glucose beverage (Glucomedics^®^, Lambra, Madrid, Spain) in 5 min. After consumption of this beverage, separate blood collections at 30 min, 60 min and 120 min follow.

For the fasting blood test in the offspring, participants are asked to fast for at least 8 h. Prior to the blood sampling, they can only drink water.

All blood measurements will be centrally analyzed in the lab at UZ Leuven to assure uniformity of the analysis. Only the glucose analyses will be done locally to avoid any delay in diagnosing diabetes. The blood samples will be stored at the local center at −20 °C for a maximum of three months before shipment to UZ Leuven. Blood samples will then be stored at −80 °C in the UZ Leuven biobank. Coefficients of variance are 1% for glucose, 6% for insulin, 2% for lipids, 2% for HbA1c and 8% for C-peptide in the UZ Leuven lab.

#### 3.3.2. Clinical Measurements

Blood pressure and heart rate are measured using a calibrated Omron automatic blood pressure monitor. Height is measured to the nearest 0.5 cm using a calibrated wall-mounted stadiometer. Weight is measured to the nearest 0.1 Kg using a calibrated portable digital scale. BMI is calculated as kg/m^2^ for women and as BMI z-score for offspring [23]. Waist circumference is measured to the nearest 0.1 cm by applying the tape directly on the skin, horizontally at the lateral level midway between the iliac crest and the lowest lateral portion of the rib cage. Hip circumference is measured to the nearest 0.1 cm over the widest part of the gluteal region. Offspring are weighed without shoes and lightly dressed. Body fat is measured by bioelectrical impedance analysis (Bodystat 1500, Bodystat Limited, Douglas, Isle of Man, Great Britain). Skinfolds are measured at three different sites (triceps, subscapular, suprailiac, measured twice at each site with calibrated calipers (Harpenden, Baty International, West Sussex, Great Britain) to the nearest 0.1 mm (if results differed by >1.0 mm, they were measured a third time)) [18]. Means of the two skinfold measurements, or the two closest measurements if three measurements were made, are used for analysis. All participating centers received specific training for the skinfold measurements in order perform these measurements correctly. In addition, instructional videos were made for skinfold measurements to refresh training if necessary.

All anthropometric measurements are taken twice, and if the differences exceed 0.5 cm or 0.5 kg for the anthropometric measurements, or 5 mmHg for blood pressure measurements, a third measurement is taken. In all analyses, the mean value of the measurements is used. The anthropometric measurements are performed by a trained nurse, physician or clinical trial assistant.

#### 3.3.3. Self-Administered Questionnaires

The following self-administered questionnaires are used:

For the mother:Self-designed questionnaire on general habits (including smoking and alcohol habits) and socioeconomic factors, as used in the BEDIP-N study [22];The Frequency Food Questionnaire (FFQ) validated for the Belgian population [24] to assess food and nutrition intake. This is a questionnaire that contains questions on portion and frequency of food and beverage consumption;The international questionnaire on physical activity (IPAQ), validated for use in the Belgian population and as used in the BEDIP-N study for the mothers [22,25]. This is a questionnaire measuring different areas of physical activity such as job-related physical activity, transportation, housework and caring for family, recreation and time spent sitting. We added a question on time watching television or playing computer games to better assess sedentary behavior;The validated 20-item Center for Epidemiologic Studies Depression Scale (CES-D) questionnaire [26] to assess symptoms of depression in the past 7 days;A self-designed questionnaire on breastfeeding and contraception as used in the BEDIP-N study [22];The validated questionnaire on general health (SF-36) [22,27] to assess quality of life;The validated Diabetes Risk Perception questionnaire [28];The validated Treatment Self-Regulation Questionnaire (TSRQ) to evaluate motivation for lifestyle change [29];The validated short version STAI-6 to measure anxiety [30];The validated Pittsburgh Sleep Quality Index to evaluate sleep quality as a risk factor for the development of glucose intolerance [31].

For the offspring (completed by the mothers):The validated FFQ for children [32] to evaluate food and nutrition intake;The validated Dutch Physical Activity Questionnaires for Children [33];The child health questionnaire—parent form (CHQ-PF50) validated to assess health-related quality of life for children [34].

For the father:Self-designed questionnaire on general habits (including smoking and alcohol habits) and socioeconomic factors as used in the BEDIP-N study [22] including data on paternal weight and BMI over time.

### 3.4. Outcomes of the Study

#### 3.4.1. Primary outcome

For mothers: A disorder of glucose metabolism: T2D defined by the 75 g OGTT and/or HbA1c, or prediabetes defined as IFG and/or IGT by the American Diabetes Association (ADA) criteria [1].

For offspring: BMI z-score as a continuous variable [23].

#### 3.4.2. Secondary Outcomes

Secondary outcomes for mothers:BMI as continuous variable and as overweight: BMI ≥ 25 kg/m^2^ and obesity BMI ≥ 30 kg/m^2^;Metabolic syndrome based on the WHO criteria [35];Insulin sensitivity measured by the Matsuda insulin sensitivity index, a well-established measure of whole-body insulin sensitivity [36], and the reciprocal of the homeostasis model assessment of insulin resistance (1/HOMA-IR) (largely hepatic measure of insulin sensitivity) [37];Beta-cell function by the HOMA-B index and the insulinogenic index divided by HOMA-IR [38], the insulin-secretion sensitivity-2 index [39], and the Stumvoll index [40]. All these measures have been validated for use in women with GDM and have been used in the BEDIP-N study [22];Adiposity (as a continuous variable) measured by the bioelectrical impedance analysis (BIA), and measured by skinfolds [41];Plasma glycated CD59 as a predictor of metabolic risk [11,13].

Secondary outcomes for offspring:Overweight and obesity defined by BMI z-score according to the WHO guidelines (resp. score >1 and >2) [23];Prediabetes and diabetes based on the fasting plasma glucose defined by the ADA criteria [1];Metabolic syndrome based on the WHO criteria [35];Insulin sensitivity by 1/HOMA-IR [37];Beta-cell function by the HOMA-B index [22];Adiposity measured by BIA and measured by skin folds [41];Weight and growth trajectory;Plasma glycated CD59 as a predictor of metabolic risk [11];Sex differences in metabolic profile in the offspring.

### 3.5. Collection of Data from the Medical Electronical Records

For the mothers, we are collecting data concerning previous pregnancies other than the one during the BEDIP-N study. The following data are collected: pre-pregnancy weight, weight in early pregnancy, weight at delivery, pregnancy outcomes, gestational weight gain, parity, medical history, current treatment, history of metabolic syndrome, history of (pre)diabetes, diabetes related complications (retinopathy, microalbuminuria, nephropathy, neuropathy), cardiovascular diseases (heart, cerebral and peripheral arterial disease).

For the offspring, we will collect the following data from their medical records: medical history, current treatment, history of (pre)diabetes, information on school attendance (which school, which school year). Data on growth and weight trajectory, and data on the development of the child, will be collected through the databases used by the Flemish health services for the normal follow-up of children.

### 3.6. Power Calculation and Statistical Analyses

#### 3.6.1. Sample Size

Since there are currently no data on the long-term metabolic risk of lesser degrees of hyperglycemia than GDM based on the GCT and 75 g OGTT using the currently recommended 2013 WHO criteria, we based our power calculation on the Canadian study by Ravi Retnakaran et al. in which women received the GCT and 100 g OGTT using the National Diabetes Data Group criteria [4]. The distribution of the patients over the groups was based on the BEDIP-N study as previously published [10]. The power calculation is performed for the primary outcome for mothers: glucose intolerance after on average five years. We aim to compare glucose intolerance as a binary outcome variable between the GDM group (3), where a 26% prevalence is assumed, and (1) normal GCT-NGT group and (2) abnormal GCT-NGT group, with an assumed prevalence of 4% and 12%, respectively, with 125 subjects in each group. Considering a chi-square test, the power for the comparisons of the primary outcome at a 5% significance level, is 99% (1 vs. 3) and 81% (2 vs. 3), respectively.

#### 3.6.2. Statistical Analyses

Differences between groups will be analyzed using linear models in the case of continuous outcomes and logistic regression models in the case of binary outcomes. Results will be presented as mean differences or odds ratios, respectively, with 95% confidence intervals.

Analyses will be performed separately and analogously for comparing (1) GDM versus non-GDM, and (2) the three gestational glucose tolerance groups. In the analyses on offspring, interaction effects between the group and the gender of the offspring will be analyzed. Such an interaction effect would mean that the differences in outcome between the groups is different for males and females. In the case of a group by gender interaction effect, results will be presented by gender. In the absence of such an interaction, the main effects for the group will be presented.

Multivariable models will be used to correct for possible confounders. Correction for confounders will be performed in a stepwise fashion. For maternal outcomes, covariate adjustment will be performed for time since pregnancy in a first step. Maternal variables during pregnancy will be added as confounders in a second step, and maternal variables during follow-up will be further added in a third step. For outcomes in offspring, covariate adjustment will be performed for the child’s age and center in a first step. Maternal variables during pregnancy will be added as confounders in a second step, and offspring variables during follow-up will be further added in a third step.

Maternal characteristics during pregnancy include variables such as age, pre-pregnancy BMI, blood pressure, and smoking. Follow-up characteristics include variables such as mothers’ age, BMI measured during the OGTT and smoking for maternal outcomes, and variables such as children’s age and BMI at the time of the clinical examination for analyses on offspring outcomes. The confounders included in each analysis will depend on the concrete outcome that is being analyzed. Correction is indicated if the confounder is known or suspected to be associated with the predictor of interest (group) as well as the outcome. Confounders will be determined a priori based on expertise and literature. If the number of indicated confounders is too large in relation to the sample size, further selection will be based on univariable analyses on the association between the confounder and the group.

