### 3.2. Recruitment and Eligibility

We aim to recruit 375 women–offspring pairs with the five largest centers who participated in the initial BEDIP study, which is approximately 21% of the initial 1800 women who received both a GCT and 75 g OGTT in the BEDIP study. Women and offspring are recruited according to three different subgroups based on the antenatal result of the GCT and OGTT in the index pregnancy (a sample of 125 in each group): GDM group; NGT on the OGTT with an abnormal preceding GCT (abnormal GCT-NGT group); NGT on the OGTT with a normal preceding GCT (normal GCT-NGT group). Abnormal GCT is defined as glucose ≥ 130 mg/dL, as we have previously shown to have an acceptable sensitivity to screen for GDM in our population (20). Additional analyses will be performed on the different subgroups stratified by a GCT ≥ 140 mg/dL to evaluate whether this leads to more pronounced differences in β-cell function and insulin sensitivity across the different groups. GDM was defined by the 2013 WHO criteria. Recruitment began in January 2021 and will end around December 2023.

Eligibility criteria:

The inclusion criteria for the mother are:Age ≥ 18 years;Participated in the completed BEDIP-N study and received both the GCT and the OGTT during pregnancy;

The inclusion criterion for the offspring is:Born at the time of participation in the BEDIP-N study.

The inclusion criterion for the father is:Biological father of the child born during participation in the BEDIP-N study.

The exclusion criteria for the mother are:Current pregnancy;Current treatment that influences glycemic status, such as high dose corticoids or incretin mimetic medication;History of bariatric surgery or any gastrointestinal surgery that alters glucose absorption (Billroth II);Inability to complete a normal study visit (incompliance, psychiatric problems);Diagnosis of type 1 diabetes or the presence of autoimmune antibodies for type 1 diabetes.

The exclusion criteria for the offspring are:Current treatment that influences glycemic status, such as high dose corticoids;Inability to complete a normal study visit (incompliance, psychiatric problems);Diagnosis of type 1 diabetes or the presence of autoimmune antibodies for type 1 diabetes.

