Studies provide no evidence yet that treating GDM in pregnancy can reduce the future risk for obesity and glucose intolerance in mothers and offspring. Reduction of macrosomia at birth was seen in women with GDM who received intensified glucose-lowering treatment, but follow-up studies of offspring showed no decline in childhood obesity or metabolic dysfunction in these children at the age of 4–10 years [42,43]. However, in an American study, sex-specific differences were seen, with a decreased frequency of impaired fasting glucose, lower fasting glucose, and lower insulin resistance in female offspring but not in male offspring [43]. Differing sensitivities to hyperglycemia in utero may result in long-term sex-specific programming. Additional studies are needed to understand the separate role and the combined potential superimposing effect of maternal hyperglycemia, maternal obesity during pregnancy and paternal BMI on the metabolic health of offspring. Moreover, data on the metabolic profile of offspring of women diagnosed with GDM according to the 2013 WHO criteria are scarce. Studies should also investigate sex differences in metabolic profiles in the offspring. With the BEDIP-N follow-up study we aim, therefore, to also evaluate potential sex differences in long-term metabolic risk across different gestational glucose tolerance groups in pregnancy.

A major strength of our study is that all women received both a GCT as well as an OGTT during pregnancy, allowing investigation of the impact of different glucose tolerance groups during pregnancy on the long-term glucometabolic risk of women and their offspring. We also have a large dataset on pregnancy and delivery outcomes for both mother and offspring. A limitation of our study is that our cohort mainly consists of Caucasian women.

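### Offspring group effects are promised by sex only if an interaction is found, so for small to moderate differences a low-powered test decides whether a stated objective gets sex-specific results

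*Protocol article*

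**What the plan says.** Section 3.6.2 states that in the offspring analyses "interaction effects between the group and the gender of the offspring will be analyzed". Two reporting branches follow. If an interaction is found: "In the case of a group by gender interaction effect, results will be presented by gender". If not: "In the absence of such an interaction, the main effects for the group will be presented". No criterion is given for deciding that an interaction is present or absent. The rule covers the offspring analyses as a whole, and so includes the offspring primary outcome in section 3.4.1, "BMI z-score as a continuous variable". The group contrasts it applies to are those of section 3.6.2, "comparing (1) GDM versus non-GDM, and (2) the three gestational glucose tolerance groups".

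Sex is not an incidental subgroup here. "Sex differences in metabolic profile in the offspring" appears among the secondary outcomes in section 3.4.2 and again in the list of objectives in section 2. The discussion repeats the aim to "evaluate potential sex differences in long-term metabolic risk across different gestational glucose tolerance groups in pregnancy".

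The power calculation in section 3.6.1 covers only the maternal primary outcome.

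**The concern.** The two-branch rule makes the reporting of a stated objective depend on a preliminary test for which the study was not sized. Three consequences follow.

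- If a real sex difference is missed, the promised presentation is a pooled group effect that averages different effects in girls and boys. The article's wording treats not finding an interaction as its absence, so readers may take this as evidence that the sexes do not differ.
- If the interaction is found, the sex-specific effects shown have been selected because their difference was large in this sample, so that difference is overestimated on average.
- For BMI z-score, the data decide whether the primary result is one pooled contrast or two sex-specific contrasts. The quantity being estimated for the primary offspring outcome is then not fixed in advance.

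**Working it through.** **The plan's own power figure (mothers only, section 3.6.1).** With n = 125 per group and a two-sided 5% test, power = Φ((|p1 − p2| − 1.96 × SE0) / SE1), where SE0 uses the pooled proportion and SE1 the separate proportions.

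- 4% v 26%: SE0 = √(2 × 0.15 × 0.85 / 125) = 0.0452; SE1 = √((0.04 × 0.96 + 0.26 × 0.74) / 125) = 0.0430; power = 99.9% (stated 99%).
- 12% v 26%: SE0 = √(2 × 0.19 × 0.81 / 125) = 0.0496; SE1 = √((0.12 × 0.88 + 0.26 × 0.74) / 125) = 0.0488; power = 80.9% (stated 81%).

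The stated figures reproduce. There is no corresponding figure for any offspring outcome or interaction.

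**Inputs for the interaction.**

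- From the article, section 3.2: "a sample of 125 in each group", three groups, 375 pairs.
- Assumed, because the article does not give them: equal sex split (125 / 2 = 62.5 per sex per group), outcome SD of 1, two-sided 5% level (borrowed from the maternal calculation), all children measured, no covariate adjustment.

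**Standard error of the sex difference in a group effect (SD units).**

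- Two groups compared, four cells of 62.5: √(4 / 62.5) = 0.253.
- GDM (125) v non-GDM (250): √(2 / 62.5 + 2 / 125) = 0.219.

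**Power** = Φ(d / SE − 1.96) + Φ(−d / SE − 1.96), where d is the true difference between girls' and boys' group effects.

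| d (SD) | Pairwise | GDM v non-GDM |
|---|---|---|
| 0.2 | 12% | 15% |
| 0.3 | 22% | 28% |
| 0.4 | 35% | 45% |
| 0.5 | 51% | 63% |
| 0.7 | 79% | 89% |

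The difference detectable with 80% power is (1.96 + 0.84) × SE: 0.71 SD pairwise and 0.61 SD for GDM v non-GDM. Power is below 50% up to about 1.96 × SE: 0.50 SD and 0.43 SD. A joint 2-df test across the three groups has 17% to 21% power at 0.3 SD, depending on whether the difference rises steadily over the groups or sits in the GDM group only. At a 10% test level, 0.3 SD gives 32% / 39%.

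**Size of the selection effect.** An interaction is significant at 5% only if its estimate exceeds 1.96 × SE, i.e. 0.50 SD (pairwise) or 0.43 SD (GDM v non-GDM). For a true d, the mean of the significant estimates is close to d + SE × φ(1.96 − d / SE) / Φ(d / SE − 1.96). At d = 0.3:

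- Pairwise: 0.3 + 0.253 × 0.296 / 0.219 = 0.64, about 2.1 times the truth.
- GDM v non-GDM: 0.3 + 0.219 × 0.335 / 0.277 = 0.56, about 1.9 times the truth.

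**What unconditional reporting would give.** The 95% interval for the sex difference would have a half-width of about 0.50 SD pairwise and 0.43 SD for GDM v non-GDM: imprecise, but unselected.

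**The case against.** Several points on the other side stand and limit the claim.

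- A reader might infer that the sex objective will get no estimate at all. The article does not support that. It says the interaction will be analysed, and section 3.6.2 promises mean differences or odds ratios with 95% confidence intervals in general. Nothing forbids reporting the interaction estimate, which is itself an estimate of the sex difference. What is missing is a promise of that estimate, or of group effects by sex, when no interaction is found.
- A reader might take 20% to 30% as the study's power. That is only the 0.3 SD case under assumptions the article does not state. Over 0.2 to 0.5 SD the range is 12% to 63%, and at 0.5 SD a true difference would be found slightly more often than missed.
- A reader might infer that the discussion expects effects in girls and not boys. It describes one American follow-up study of GDM treatment in which glycaemic measures improved in female offspring only. The article's own aim is neutral as to direction, and that study does not concern group differences in BMI z-score.
- Reporting both sexes is not free. Many offspring outcomes, two group comparisons and three adjustment steps make a long list, and adjusted odds ratios for rare outcomes could be unstable with about 62 children per cell.

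Two further defences carry less weight. Testing the interaction first is common practice, and it does guard against over-reading incidental subgroups, but here sex is a pre-stated objective. A separate analysis plan could set the test level, but the conditional rule is already fixed in the article. Reporting by sex regardless would change that rule, not merely add detail to it.

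**Conclusion.** The concern holds in this limited form and should be addressed. Section 3.6.2 promises sex-specific group effects only when an interaction is found, while the article names sex differences in the offspring as an objective and secondary outcome. With 125 children per group, an equal sex split, SD 1 and a two-sided 5% test, the deciding test has less than even power for true differences up to about 0.50 SD pairwise or 0.43 SD for GDM v non-GDM. In that range the rule would more often than not leave the objective without promised sex-specific effects, and when it does show them the sex difference would tend to be overestimated. An unequal sex split, missing blood samples for the blood-based outcomes, and binary outcomes would lower the power; a looser test level would raise it somewhat. The form in which BMI z-score is reported also depends on the data. The maternal primary outcome and its power calculation are unaffected.

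**What to change.** In section 3.6.2, replace the two conditional sentences with a fixed rule:

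1. The main-effect model is the primary analysis of BMI z-score, whatever the interaction test shows.
2. For BMI z-score and the key continuous metabolic outcomes, named in advance, the interaction estimate and the group effects in girls and in boys are always reported with 95% confidence intervals and labelled exploratory.
3. A non-significant interaction is interpreted as inconclusive, not as absence of a sex difference.

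The change uses data already being collected. Its cost is extra tables and wide intervals. Rare binary outcomes should be left out of the sex-specific reporting or given as counts only.

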## 3. Methods and Analysis

### 3.1. Study Design and Setting

This is a Belgian multi-centric prospective follow-up study of the BEDIP-N cohort (Figure 1). The BEDIP-N study was a multicentric prospective cohort study to compare different screening strategies for GDM, which has been previously described in detail [10,20,21,22]. In this follow-up study, five of the original seven centers are participating (University hospital of Leuven (UZ Leuven), Antwerp University Hospital, OLVZ-Aalst, OLVZ-Asse and Imelda Bonheiden). UZ Leuven is the coordinating center. Of all participants in the BEDIP study, 95% consented to be contacted within 10 years after the study end to potentially participate in a follow-up study. Women who consented to be contacted, are invited by email, phone or letter to participate in the BEDIP-FUS study. Our study is registered in ClinicalTrials.gov as NCT04429958 since June 2020 and was approved by the Medical Ethical Committees of all participating centers.

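### The maternal models omit center, although the glucose values that decide most of the maternal primary outcome are measured in local labs; the offspring models include it

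*Protocol article*

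**What the plan says.** **Measurement.** Section 3.3.1 sets central analysis as the rule: "All blood measurements will be centrally analyzed in the lab at UZ Leuven to assure uniformity of the analysis". It then makes one exception: "Only the glucose analyses will be done locally to avoid any delay in diagnosing diabetes". Section 3.1 says that "five of the original seven centers are participating".

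**Outcome.** In Section 3.4.1 the maternal primary outcome is type 2 diabetes or prediabetes. Diabetes is "T2D defined by the 75 g OGTT and/or HbA1c". Prediabetes is impaired fasting glucose and/or impaired glucose tolerance, so it rests on glucose alone. Section 3.4.2 adds insulin-sensitivity and beta-cell indices that also use glucose.

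**Adjustment.** Section 3.6.2 fixes the first covariate step in two parallel sentences. For mothers: "For maternal outcomes, covariate adjustment will be performed for time since pregnancy in a first step". For offspring, the step covers the child's "age and center in a first step". Maternal steps 2 and 3 add maternal variables from pregnancy and then from follow-up. The examples are age, BMI, blood pressure and smoking.

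**Recruitment.** Section 3.2 sets 125 women per glucose group overall and states no balance of the groups within centers.

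**The concern.** The plan treats uniformity of blood analysis as important enough to centralize, then exempts the analyte on which the maternal primary outcome mainly depends. That exemption has a stated practical reason and is not itself the problem. What is missing is its counterpart in the analysis. A yes/no outcome defined by a glucose cut-off responds to small calibration offsets, because women close to the cut-off change category.

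If one center reads slightly high and supplies a larger share of one glucose group than of another, that group's prevalence rises for a reason unrelated to gestational glucose tolerance. A center term makes the comparison within labs and removes most of this. The plan secures that protection for offspring but not for mothers. The comparison with least room for distortion is GDM against abnormal GCT-NGT, whose stated power is 81%.

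**Working it through.** **1. The plan's own figures.** Section 3.6.1 assumes prevalences of 4%, 12% and 26% with 125 women per group, a chi-square test and a 5% level (taken as two-sided). Power = Φ[(d − 1.96·SE0)/SE1], with SE0 from the pooled and SE1 from the separate proportions.
- 12% vs 26%: d = 0.14; SE0 = √(2·0.19·0.81/125) = 0.0496; SE1 = √((0.12·0.88 + 0.26·0.74)/125) = 0.0488; power = Φ(0.875) = 80.9% (stated 81%).
- 4% vs 26%: d = 0.22; SE0 = 0.0452; SE1 = 0.0430; power = 99.9% (stated 99%).

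Both stated figures reproduce and are not in dispute. The calculation contains no center term.

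**2. Sensitivity of a cut-off to a lab offset.** Assumed, not in the documents: fasting glucose N(90, 8) mg/dL and a cut-off of 100 mg/dL. A proportional offset k multiplies mean and SD, so the share at or above the cut-off is 1 − Φ[(100 − 90k)/(8k)].

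| Offset | Share at or above 100 |
|---|---|
| none | 10.6% |
| +1% | 13.0% |
| +2% | 15.7% |
| +3% | 18.8% |

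Suppose the center reading 3% high supplies 50% of one group and 25% of the other. The shift in the contrast is (0.50 − 0.25) × (0.188 − 0.106) = 0.02, or about 2 points against the planned 26 − 12 = 14. With equal shares the first factor is zero.

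**3. The same question on the odds-ratio scale.** This is a second illustration with its own assumptions: the outcome is a threshold on one normal glucose value with SD 8 mg/dL, and two types of lab read b/2 above and b/2 below the truth. A true prevalence p becomes 1 − Φ[Φ⁻¹(1 − p) ∓ b/16]. For 12% vs 26% the true odds ratio is (0.26/0.74)/(0.12/0.88) = 2.58. The mix is the percentage split of each of the two groups between the lab types. The range covers both directions of imbalance; power is for the unfavorable one.

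| Mix, one group vs the other | b = 2 mg/dL: crude OR | Power | b = 4 mg/dL: crude OR | Power |
|---|---|---|---|---|
| 50/50 vs 50/50 | 2.55 | 81% | 2.49 | 79% |
| 60/40 vs 40/60 | 2.34 or 2.79 | 73% | 2.10 or 2.97 | 62% |
| 70/30 vs 30/70 | 2.14 or 3.06 | 63% | 1.77 or 3.55 | 41% |

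Within a lab type the odds ratio stays between 2.46 and 2.73 even at b = 4. Comparing within center would therefore remove most of the distortion.

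**4. Room for a center term.** Expected events: 125 × (0.04 + 0.12 + 0.26) = 5 + 15 + 32.5 = 52.5. Five centers need 4 terms. A three-group model with time and center has 2 + 1 + 4 = 7 parameters, or 52.5/7 = 7.5 events per parameter. Without center it has 3, or 17.5 per parameter.

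**The case against.** Four arguments stand on the other side.

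- **The confounder rule is open.** Section 3.6.2 lets the confounder set depend on the outcome, and indicates correction for anything known or suspected to relate to both group and outcome. Center could qualify, so it is unlisted rather than excluded. This stands in part. Steps 2 and 3 are worded as maternal variables, every example is a personal characteristic, and the list may be cut by univariable selection if it grows too long. The rule permits center but does not secure it, whereas the offspring sentence does.
- **The bias is conditional.** It needs both a calibration difference and an uneven group mix. The documents show neither, and silence on balance is not evidence of imbalance. The 2-point illustration is also smaller than the 4.9-point standard error of the planned 12% vs 26% difference (0.0488 above). This stands fully and limits the claim to a precaution.
- **Sparse events.** About 52 events, only about 5 of them in the normal GCT-NGT group, leave little room for extra terms. A linear model for BMI z-score has no such limit. This could explain the asymmetry, although the article does not say so. It is a real cost.
- **The HbA1c route is central** and so is unaffected. This stands, but HbA1c is no part of the prediabetes definition.

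A reader might also infer that the plan adjusts the wrong population. The documents do not support that: offspring height and weight are measured at each site (Section 3.3.2), and offspring secondary outcomes use fasting glucose, which is local too. Center belongs in the offspring models. Nor does the statement "Coefficients of variance are 1% for glucose" settle anything. It is attributed to the coordinating lab, and a coefficient of variation describes precision, not calibration between labs.

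**Conclusion.** The point holds as a gap in the maternal models. Center is fixed in the offspring first step, appears in no maternal step, and no reason is given, although locally measured glucose decides most of the maternal primary outcome.

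It would be tempting to conclude that the primary comparison is confounded. The documents do not establish this, because they report neither the agreement between labs nor the group mix by center. Under the assumed inputs the contrast moves by about 2 points against 14. In the odds-ratio illustration, uneven mixes move 2.58 to about 2.1–3.1 for a 2 mg/dL lab difference and 1.8–3.6 for 4 mg/dL. With equal mix there is only slight attenuation. These figures show what could happen and are not estimates for this study. The change is worth making because it is cheap and protects the primary contrast where the planned power is only 81%.

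**What to change.** In Section 3.6.2, change the first maternal step to time since pregnancy and center, matching the offspring step. Apply it to the primary outcome and to the glucose-derived secondary outcomes, in both the GDM versus non-GDM and the three-group analyses. If events are sparse, merge the smallest centers or use a random intercept for center, and state in advance which will be used. If the investigators prefer to leave center out, the section should give the reason.

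The cost is one phrase. No new data are needed, because the offspring models already require center for the same mother–child pairs. Statistically it takes up to 4 degrees of freedom against about 52 expected events, or one variance term with a random intercept, though a variance estimated from five centers will be imprecise. It leaves less room for the covariates of steps 2 and 3.
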